#### Gait

The primary mechanistic outcome is maximal knee compressive force; secondary outcomes include internal knee abduction moment and AP shear force [55-59]. A 25-reflective marker set, 6-camera Motion Analysis System (100 Hz), and 2, 6-channel force plates (AMTI, Newton, MA. 1000 Hz) obtain 3D kinematic and kinetic gait data. The former will be acquired using Cortex 3.0 software (Motion Analysis Corporation, Santa Rosa, CA) and a Butterworth low-pass filter (6 Hz cutoff). For each participant, 3 successful trials are analyzed; i.e., within ±3.5% of the participant’s freely chosen speed, and the entire foot must contact the force plate in a visually normal stride. Smoothed coordinate data, ground reaction, and gravitational and inertial forces will inform an inverse dynamics model to calculate 3D moments and forces at the hip, knee, and ankle joints using Visual 3D Standard 4.0 clinical gait analysis software (C-Motion, Germantown, MD). These moments and forces will be used in the knee model developed by DeVita et al. [60] for use in knee OA subjects [58,59]. Model-predicted knee-compression force was also a primary outcome in IDEA. Our test-retest reliability intraclass correlations (ICC) for 21 knee OA patients with mean age 65.7 yrs (SD = 5.8) were r = 0.86 for internal peak knee extensor moment, r = 0.94 for internal peak abductor moment, and r = 0.95 for peak knee compressive force [61]. A detailed explanation of our model can be found elsewhere [62].

Numerous biomechanical-neuromuscular models exist that predict knee joint forces during locomotion. Many of these models predict highly similar results, strengthening the confidence researchers have in these models [63-65]. True biomechanical model validation is difficult and most predicted results have not been compared to measured knee joint forces, a gold standard for model validation. Recently, Fregly et al. [66] have made available measured *in vivo* knee joint force data during walking along with all pertinent biomechanical data for the purpose of validating biomechanical models predicting knee joint loads. These data come from individuals with instrumented knee joint prostheses and are available through the website, https://simtk.org/home/kneeloads. We used their biomechanical gait data as input for our model to predict knee joint forces from five walking trials and then compared our results to Fregly’s actual measured values from the same subjects. Our predicted values were highly similar to the measured values with the predicted first and second maximum compressive forces within 7% and 3% of the observed values, respectively (Figure 3).

**Figure 3 F3:**
[figure not shown]
Comparison of peak knee compressive forces derived from our musculoskeletal model (predicted) using Fregly et al. data as input, and the measured value from an instrumented prostheses (measured) of the same subjects.

#### Mobility

Our measure of mobility is 6-min walk distance, with a 3-month test-retest reliability of 0.86 [67].

#### Health-Related Quality of Life (HRQL)

The SF-36 [68] is the most widely used and carefully validated measure of HRQL. It yields two broad summary scores: physical health and mental health.

#### Body composition

Dual-energy x-ray absorptiometry (DXA) (GE Healthcare iDXA Digital Densitometry) is used for measurements of bone mineral density (BMD) and body tissue composition including whole body changes in total fat (FM) and lean (LM) mass [69-71]. Percent coefficients of variation (%CV) are 1.2% for whole body FM; 0.5% for whole body LM; 0.9% for whole body BMD; 1.2% for posterioranterior (PA) spine BMD; and 0.9% for total hip BMD.

#### Thigh composition

A secondary outcome is the measurement of thigh skeletal muscle and adipose tissue using volumetric non-contrast enhanced computer tomography (CT) (VCT 64, GE Healthcare Waukesha, WI). Participants will be placed supine on the CT couch with their legs held in a neutral position by dedicated Velcro straps. A calibration phantom (Image Analysis, Columbia, KY) with known CT densities for fat, water, and calcium is placed in the scan fields of view (FOV) posterior to the legs. A 2-dimensional topogram is obtained covering from the pelvis to the knees. A single helical scan series is performed starting at the femoral head and ending below the knee joint in the tibial plateau. Technique for the scan includes: helical mode, 120 KV, 150 mAs, with reconstruction of both legs at 5 mm slice thickness and 50 cm display field of view (DFOV). Additional reconstructions are performed using the same exposure to the participant to obtain sets of images using thinner slices (1.25 mm and 0.625 mm) using both standard and bone kernels to optimize image quality. Each femur has a set of high-resolution 30-cm dfov targets for potential future analysis of cortical bone structure.

#### CT image analysis software and protocol

The topogram of the femur is measured from the greater tuberosity of the femur to the inferior aspect of the medial femoral condyle. This length is trisected, and the junction between the proximal and mid-third is the landmark for measurement. Measurements of right and left thigh composition are performed using the slices that start at the location 25 mm above and the end 25 mm below this point, providing a sampling length of 50 mm along the long axis of the femur (e.g. head to foot). CT images are analyzed (reader masked to treatment group) on a medical imaging workstation with custom plugins to measure the volume of the entire thigh, thigh musculature, and intermuscular fat. Test-retest reliability on the thigh CT scans of a quality control sample of START participants (n = 10) re-analyzed an average of 3.7 months apart was: total thigh volume, ICC = 0.99; total fat volume, ICC = 0.99, and total muscle volume, ICC = 0.99.

#### Blood and urine sample collection

Blood samples (50 ml per visit) for assessing biomarkers are collected via venipuncture at a specific time in the morning at least 2 hours after rising and after a *10-hour overnight fast* at baseline and at 6- and 18-month assessment visits. Urine samples (second am void, 20 ml per visit) are collected in 250 ml specimen cups by each participant for analysis of new and emerging OA biomarkers. Serum, plasma, and urine are aliquoted and stored at -80°C until analysis of our pre-chosen biomarkers (see below) at the end of the study. Aliquots are also stored long-term to test for promising new inflammatory and OA biomarkers that may become available after the study.

#### Inflammatory markers

IL-6, tumor necrosis factor-alpha (TNFα), and soluble TNF receptor 1 (sTNFR1) were chosen for their known implication in OA [72-77]. They have been shown to change with 1 year of moderate strength training [78]. *IL-6 is our primary inflammation measure.* All inflammatory marker assays are performed in the WFSM ELISA Core Laboratory. All samples are measured in duplicate, using the average for analyses. Commercially available (R&D Systems, Minneapolis, MN) enzyme-linked immunosorbent assay (ELISA) kits are used: high-sensitivity Quantikine® for IL-6. In our laboratory, inter- and intra-assay coefficients of variation (CV) for IL-6 are 5.4% and 3.5%, respectively; for TNFα, 11.8% and 6.2%, respectively; and under 5% for the soluble receptor assays

#### OA Biomarkers

There is a lack of gold standard biomarkers for OA and so the choice of biomarkers that will be measured will be based on the most recent findings available at the completion of the trial. Possible markers could include serum COMP (AnaMar Medical, Uppsala, SW) and urine markers of collagen degradation such as C2C-HUSA (Ibex Technologies, Montreal, CN).

#### Muscle function tests

##### Strength

Knee flexion/extension concentric strength is assessed at baseline, 6, 12, and 18 months using a Humac NORM isokinetic dynamometer (Computer Sports Medicine Inc, Stoughton, MA) set to 30 deg^.^s^-1^. Strength test-retest reliability for 10 participants tested twice in our lab, 7–10 days apart, had an ICC of 0.93 for both concentric knee flexion and extension strength. Since we suggest that intensive strength training can reduce knee-joint loads by counterbalancing the external knee-adductor moment with strong hip abductors, we also measure hip-abductor concentric strength at 30 deg^.^s^-1^ (ICC = 0.99). Knee strength is measured with the participant in a seated position; hip abductor strength is measured in a side lying position.

##### Power

The Nottingham power rig is used to measure bilateral leg extensor power because it correlates well with such functional measures as chair-rise, stair-climbing, and walking speed in elderly subjects [79]. This measurement is safe and acceptable for all age groups [79,80].

#### Medications

A questionnaire adapted from the Atherosclerosis Risk In Communities (ARIC) [81] study and widely used in field research and our studies is designed to obtain information (during SV1 and FU visits) about all prescription and over-the-counter medicines and supplements used during the 2 weeks prior to interview.

#### X-ray

Bilateral PA weight-bearing knee x-rays using a positioning device (SynaFlexer™, Synarc Inc., San Francisco, CA) and the modified Lyon-Schuss technique [82] are used to identify tibiofemoral (TF) OA and skyline views to identify PF OA. The former is repeated at 18 months to assess changes in joint-space width (JSW). Radiographs are evaluated using the K-L score of 0–4 to assess disease severity as we have described and we include only participants with a score of 2 or 3 in at least one knee (KL score = 4 is acceptable in the contralateral knee). We exclude people with severe PF OA (JSN = 3 on a 0–3 scale using the OARSI atlas) and control for severity (none-to-moderate) in statistical analyses. We define medial TF disease based on our previous definitions [83], and participants with lateral > medial joint space narrowing are excluded.

The knee PA protocol includes positioning the participant standing and facing the Bucky or cassette holder with the x-ray beam centered on the joint line angulated caudally 10 degrees. The x-ray is repeated at 5 and 15 degrees and the most acceptable image (based upon alignment of the medial tibial plateau) is used for analysis. Criteria include good contrast/exposure, optimal visualization of the articular surfaces with the floor of the medial tibial plateau clearly delineated, and both knee joints included and centered on the film.

To assess alignment, a full-length AP radiograph of each lower extremity is obtained at baseline with participants positioned following Sharma et al. [84]. Mechanical alignment is the measure of the angle formed by the intersection of the lines connecting the centers of the femoral head and intercondylar notch and the centers of the ankle talus and tibial spines, with neutral angles between 0-2° varus, varus knee angles >2° inward, and valgus angles >0° outward*. The range of eligible knee angles is -2**°**valgus to 10*° *varus.*

Disease progression is defined as change in x-ray medial TF JSW. A physician, masked to treatment group, measures JSW using automated computerized software. The software automatically delineates the joint space contour with the help of an edge-based algorithm. The area of measurement of minimum JSW is defined by 2 vertical lines and 2 horizontal lines obtained by a single click on the nonosteophytic outer edge of the medial femoral condyle and a single click on the inner edge of the medial tibial plateau close to the articular surface. Within these landmarks, the delineation of the bone edges of the medial femoral condyle and medial tibial plateau floor, in addition to the minimum JSW, are automatically obtained [85].

#### Additional questionnaires

Physical Activity Scale for the Elderly (PASE) [86], Center for Epidemiologic Studies Depression Scale (CES-D) (92), and a self-efficacy for adherence measure [87] are used to assess physical activity, depression, and self-efficacy at baseline and follow-up. The Montreal Cognitive Assessment (MoCA) is used to measure cognitive functioning at baseline; a score ≥ 20 is required for study inclusion. The Digital Symbol Substitution Test (DSST) will be used to measure cognitive functioning.

#### Adverse event collection and reporting

An adverse event (AE) is defined as any unfavorable and unintended diagnosis, sign, symptom, or disease temporarily associated with the study intervention, which may or may not be related to the intervention. Non-serious AEs will be reported by the study staff to the project manager and principal investigator within 7 days of notification of the event. The study physician will review each non serious AE on a weekly basis that will be included in the NIAMS safety officer report that is submitted semi-annually. A serious AE (SAE) is any untoward medical occurrence that results in death, is life-threatening, requires or prolongs hospitalization, causes persistent or significant disability/incapacity, results in congenital abnormalities, or represents other significant hazards or potentially serious harm to research participants or others. Study staff will report SAEs to the project manager, study physician, and the principal investigator within 24 hours of notification. NIAMS will be notified within 24 hours subsequent to notification of the principal investigator.

### Timeline

Recruitment for each of 10 waves takes 3 months with an average of 37.2 participants/wave; an average of 12.4 participants are randomized/month for 30 months.

### Randomization

A stratified block randomization with block size unknown to investigators and staff ensures equal accrual to each study arm. Prestratification balances pretrial BMI values (20.0-24.9, 25.0-29.9, 30.0-34.9, 35.0-39.9, 40.0-45.0 kg^.^m^-2^) and gender, which could predict intervention effect and associations between secondary outcome variables.

### Data management

Data are collected on hard copy forms and transformed to an electronic database. We use a web-based management system to assure integrity and validity. Dynamic reports and periodic statistical analyses monitor quality. A participant-based inventory system tracks recruitment, retention, adherence, and missing data from entry through exit, close-out, and lock-down of final datasets. Our team developed a similar database for the IDEA study.

### Statistical considerations

#### Statistical analyses

All primary analyses are based on the intention-to-treat method in which each participant is included in the initial randomization group regardless of adherence. START stratification factors, baseline BMI, and gender are included in all statistical models, so the analysis matches the design, and the estimated variance is not biased. Assumptions are verified for all models, and appropriate transformations used when necessary.

##### Primary aim

The primary aim is the treatment effect on knee pain and maximal compressive force at 18 months. These and all other repeated measures continuous outcomes will be assessed using a mixed effects model including time (6 and 18 months), treatment group, the time × treatment interaction, and further adjusted for gender, baseline BMI, and baseline values of the outcome (i.e., baseline knee pain for knee pain model, baseline compressive force for compressive force model). The treatment effects at 18 months are tested by applying contrast statements to the mixed model, and maximum-likelihood techniques will be used to estimate parameters under the assumption of an AR(1) covariance structure. Each primary outcome will be analyzed at the Bonferroni-adjusted 0.025 level of significance, and pairwise comparisons between intervention groups at 18 months will use a 0.0083 two-sided level of significance (2 outcomes, 3 interventions) [88]. Preliminary analyses are conducted to check the shape of the distributions and variances between groups and as a function of the covariates to ensure residuals are approximately normally distributed. Regression diagnostics and residual plots help find appropriate transformations if necessary. In subsequent models, we will control for possible confounders, including PF OA severity (none to moderate) and use of medications, such as analgesics, NSAIDs, bisphosphonates, and glucosamine/chondroitin sulfate. Because we exclude subjects with severe PF OA and medication has only modest efficacy in OA, we do not expect significant confounding by these variables.

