### Measurements

#### Screening and follow-up visits

Those who are eligible after prescreening (PSV) sign an informed consent and attend 2 screenings (SV) and a randomization visit (RV). All 372 participants are measured at baseline, 6-, 12-, and 18-month follow-ups (FU) (Figure 2 and Table 3).

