**Figure 2 F2:**
[figure not shown]
Participant eligibility and screening flow chart.

**Table 3 T3:** Data-collection visits

**Measurements**	**PSV**	**SV1**	**SV2**	**RV**	**FU6**	**FU12**	**FU18**
randomization				x			
informed consent		x					
eligibility questionnaire	x						
medical history	xc	x			x	x	x
WOMAC		x	x		x	x	x
PASE scale		x			x	x	x
MoCA		x			x	x	x
CES-D		x			x	x	x
SF-36 (general health, quality life)		x			x	x	x
Self Efficacy		x			x	x	x
6-min walk		x			x	x	x
Demographics		x					
Brief physical exam		x					
Medication Form		x			x	x	x
Knee A-P x-ray		x					x
Knee x-ray skyline view		x					
Full length lower extremity x-ray		x					
height	xc	x					
weight	xc	x			x	x	x
Waist/Hip circumference			x		x	x	x
DXA			x				x
CT scans: thigh				x			x
Biomarkers: blood				x			x
Biomarkers: urine				x	x		x
Gait Analysis			x		x		x
Muscle function tests: Power, Strength			x		x	x	x

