#### Western Ontario McMasters Universities Osteoarthritis Index (WOMAC)

Self-reported pain (primary clinical outcome) and physical function are measured using the Likert version of WOMAC [53]. The pain index assesses participants’ pain on a scale, ranging from 0 (none) to 4 (extreme). The pain subscale consists of 5 items and total scores can range from 0–20, with higher scores indicating greater pain. This instrument is recommended by the Osteoarthritis Research Society International as the health status measure of choice for older adults with knee OA. It has been validated for use in orthopaedic and pharmacologic interventions [53,54]. The pain subscale will be used only as a screening tool during SV1 (pain must be > 3). It will also be administered to the eligible participants at SV2 and each scheduled follow-up visit.

For physical function, the Likert version asks participants to indicate on the same scale from 0 (none) to 4 (extreme) the degree of difficulty experienced performing activities of daily living in the last 48 hours due to knee OA. Individual scores for the 17 items are totaled to generate a summary score that can range from 0–68, with higher scores indicating poorer function.

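### The pain model fixes time at 6 and 18 months and so leaves out the 12-month WOMAC pain score, which is collected anyway and would make the missing-at-random assumption easier to defend

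*Protocol article*

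**What the plan says.** The Primary aim section sets the target: "The primary aim is the treatment effect on knee pain and maximal compressive force at 18 months". It then gives one model for everything measured repeatedly. "These and all other repeated measures continuous outcomes" "will be assessed using a mixed effects model including time (6 and 18 months), treatment group", with a time-by-treatment interaction and adjustment for gender, baseline BMI and the baseline outcome value. Estimation is by likelihood: "maximum-likelihood techniques will be used to estimate parameters under the assumption of an AR(1) covariance structure".

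The visit schedule is wider than that time factor. Under Screening and follow-up visits: "All 372 participants are measured at baseline, 6-, 12-, and 18-month follow-ups (FU". The WOMAC section says of the pain subscale: "It will also be administered to the eligible participants at SV2 and each scheduled follow-up visit". Table 3 marks month 12 for WOMAC, PASE, MoCA, CES-D, SF-36, self-efficacy, 6-minute walk, weight, waist/hip circumference and muscle function. The Strength section agrees: "Knee flexion/extension concentric strength is assessed at baseline, 6, 12, and 18 months". In Table 3 the "Gait Analysis" row has months 6 and 18 but no month 12. Urine has the same pattern, and the blood and urine section places blood at baseline, 6 and 18 months.

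The Missing data section relies on missing at random. It lets variables from earlier visits that predict loss enter the models. If informative censoring occurs, it falls back on comparing complete-data, multiple-imputation and censoring-model analyses. It does not mention month-12 outcomes, and the article does not explain why month 12 is left out of the model.

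**The concern.** The 6/18 time factor fits compressive force, the other primary outcome, because gait is not measured at month 12. Applied to every repeated outcome, it removes a visit from the pain model for no stated reason.

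The plan allows for 20% loss by month 18. In a likelihood-based repeated-measures model, participants without an 18-month value inform the 18-month mean through their earlier responses. Under the plan's own AR(1) structure, month 6 adds nothing about month 18 once month 12 is known. For anyone seen at month 12 and lost afterwards, the omitted response is therefore the one that matters most. A participant who missed month 6, attended month 12 and missed month 18 has no response in the model at all, which sits badly with the intention-to-treat statement.

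Differential, pain-related loss is conceivable. The exercise arms train three times a week for 18 months, while the control arm meets every two weeks and later monthly. The Discussion also reports a widespread belief that high-intensity training may worsen pain. If participants in one arm left because pain had risen by month 12, a model without that visit would make that arm's 18-month pain look too low.

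**Working it through.** **1. The plan's own figures.** The pairwise level is 0.05/6 = 0.0083, as stated. For the secondary effect size of 0.46 at the 0.0167 level and 80% power, n = 2(2.393 + 0.842)²/0.46² = 98.9, or 99 per group. Then 99/0.8 = 123.75, or 124 per group and 372 in total. The stated sample size is reproduced. At the 0.0083 level with 99 per group, the detectable standardised difference is (2.640 + 0.842) × √(2/99) = 0.495.

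**2. An SD for pain (inferred, not stated).** If 1.12 points is 18%, the reference mean is 1.12/0.18 = 6.22. The detectable 17.6% is then 0.176 × 6.22 = 1.095 points, and the SD is 1.095/0.495 = 2.2.

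**3. Precision.** Assumptions that are not in the document: correlation between visits six months apart (ρ) of 0.3 to 0.7; AR(1) or compound symmetry; 20% loss by month 18.

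When all loss falls after month 12, the variance of an arm's 18-month mean is (σ²/124) × [(1 − R²)/0.8 + R²]. Here R² is the squared multiple correlation of month 18 with the earlier visits in the model.

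The most favourable case is AR(1) with ρ = 0.7:
- 6/18 model: R² = 0.49² = 0.2401. The bracket is 0.7599/0.8 + 0.2401 = 1.190, an effective n of 124/1.190 = 104.2.
- 6/12/18 model: R² = 0.7² = 0.49. The bracket is 0.51/0.8 + 0.49 = 1.1275, an effective n of 110.0.
- Variance reduction: 1 − 1.1275/1.190 = 5.3%. Power at d = 0.495 rises from 0.824 to 0.848.

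Over the whole grid:

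| Timing of the 20% loss | Variance reduction from adding month 12 |
|---|---|
| Mostly early (12/5/3% before months 6/12/18) | 0.2-0.9% |
| Even (6.7% in each interval) | 0.4-2.0% |
| All after month 12 | 1.0-5.3% |

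**4. Bias.** Assumptions: in one arm, 20% are lost, all after month 12, with log-odds of loss rising by 0.5 to 1.0 per SD of month-12 pain; ρ from 0.4 to 0.7. The table gives the large-sample bias in that arm's 18-month mean, from simulation with unrestricted regression on the earlier visits.

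| Correlation structure | 6/18 model | 6/12/18 model |
|---|---|---|
| AR(1) | −0.03 to −0.07 SD | about 0 |
| Compound symmetry | −0.02 to −0.05 SD | about 0 |

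In points this is 0.02 × 2.2 = 0.04 up to 0.07 × 2.2 = 0.15. Against the planning difference it is 0.044/1.12 = 4% up to 0.154/1.12 = 14%. Against the standard error of a pairwise contrast, 2.2 × √(2/99) = 0.31, it is about 0.14 to 0.5 standard errors.

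**5. Covariance.** With two visits, AR(1) has one correlation and places no constraint on it. With three equally spaced visits it forces the 6-18 correlation to be the square of the adjacent one: 0.49 when ρ = 0.7, where compound symmetry would have 0.7. The near-zero bias in step 4 was obtained without that constraint, so it does not carry over automatically to a three-visit AR(1) model.

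**The case against.** The strongest reply is the Missing data section. A reader might infer from the 6/18 time factor that missing at random must hold given 6-month pain alone. The document does not support that, because previous-visit variables found to predict loss may enter the models. In the scenario of step 4, month-12 pain is such a variable. Multiple imputation, which could also use it, is held in reserve. This stands, and the bias in step 4 is therefore that of the 6/18 model without the provision. It does not remove the point. Month-12 pain is not named. Entered as a fixed covariate, it would adjust for a post-randomisation value, absorb part of the treatment effect, and exclude those who missed the visit. As a response in the model, it does none of these.

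A reader might also infer that the 18-month contrast is biased in favour of exercise. That needs loss after month 12 that is driven by pain and differs by arm. Similar mechanisms largely cancel, and one of the three pairwise tests compares the two exercise arms with each other. Earlier loss shrinks the effect, because month 12 helps only those who attended it.

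Nor is gait the only outcome without month 12. Urine has none, nor has blood, and x-ray, DXA and CT have no interim visit.

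Finally, the hypotheses are framed at 6 and 18 months. That explains which contrasts are reported. It is no reason to leave the intermediate response out of the likelihood.

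**Conclusion.** The point holds as a moderate-to-minor weakness. The plan specifies a pain model that omits response data it already collects, and so rests on a less credible missing-at-random assumption than it needs to. Sample size, significance levels and the 18-month target are unaffected, and the compressive-force model is correctly specified at 6 and 18 months.

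The precision gain is small. The bias at stake is at most about half a standard error of a pairwise contrast, and that only when all loss follows month 12 and is pain-driven in one arm. The correlations, the timing of loss and the dropout slopes are assumptions, and the SD of 2.2 is inferred. If baseline adjustment makes the residual SD smaller, the figures in points shrink with it. None of this shows that the trial's result would be biased. It shows an avoidable exposure on a co-primary outcome.

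**What to change.** In the Primary and Secondary aims text:

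- Use categorical time at 6, 12 and 18 months for WOMAC pain and for every continuous outcome that Table 3 collects at all three visits: function, SF-36, 6-minute walk, PASE, CES-D, self-efficacy, weight, waist/hip circumference and muscle function.
- Use an unstructured covariance for these three-visit models in place of AR(1).
- Keep 6 and 18 months for outcomes without a month-12 visit: gait, and the blood and urine biomarkers where they are collected at 6 and 18.
- Keep the 18-month contrast as the primary test, at the stated levels.
- State that month-12 values enter as responses, not as fixed covariates.

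MoCA should be reconciled at the same time: Table 3 marks it at months 6 and 12, while the Secondary aims section treats it as measured at baseline and 18 months only.

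The cost is a wording change and a few more covariance parameters, best made before any unblinded analysis. No visit, measurement or participant is added.

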##### Missing data

If missing data are related to outcomes, our results will be slightly biased. Our models include variables from previous visits determined to predict loss to satisfy Little and Rubin’s [89] conditions for data considered Missing at Random (MAR). If “informative censoring” occurs, we will compare analyses using participants with complete data, multiple imputations, or explicit modeling of the censoring mechanism [90,91].

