#### Sample-size calculations

##### Primary outcomes

A total sample of 372 (124/group) provide 80% statistical power to detect differences ≥17.6% in pain and ≥9.6% in maximal compressive force at the 2-sided 0.0083 significance level with 80% retention (2-sample *t*-test, Nquery Advisor). Standard deviations for pain and maximal compressive force were obtained from the START pilot (unpublished) and ADAPT [58,59] which measured the same outcomes and used similar patient populations; with mean differences of 1.12 (18%) and 657 N (20%), respectively.

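### The primary mixed model gives the baseline outcome one slope for 6 and 18 months; adding baseline × visit would protect the 18-month contrast at almost no cost

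*Protocol article*

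**What the plan says.** The Primary aim section of the protocol article specifies a "mixed effects model including time (6 and 18 months), treatment group, the time × treatment interaction". The model is then "further adjusted for gender, baseline BMI, and baseline values of the outcome". Parameters are estimated by maximum likelihood "under the assumption of an AR(1) covariance structure". The same model is to serve all other repeated continuous outcomes, and the Secondary aims section carries the adjustment set over.

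The target is the later visit: "The treatment effects at 18 months are tested by applying contrast statements to the mixed model". On significance, "pairwise comparisons between intervention groups at 18 months will use a 0.0083 two-sided level of significance".

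Time × treatment is the only interaction named. The Statistical analyses section promises that model assumptions will be checked. The Missing data section says that variables predicting loss will be put into the models to support missing at random. Neither names a baseline × time term.

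**The concern.** Baseline is 6 months before one modelled visit and 18 months before the other. A shared slope is a compromise between the two visits, while the primary test uses only the second. If the true slope is lower at 18 months, the model over-corrects there.

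Two things follow. Residual variance at 18 months rises, which costs some power. And if the participants still present at 18 months differ between arms in mean baseline pain or force, the over-correction does not cancel in the contrast. That can happen under missing at random, because dropout driven by an observed baseline value is missing at random. Likelihood estimation is protected only if the mean model is right, and a predictor of loss entered with the wrong slope does not give that protection.

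Differential loss is conceivable here. The training arms attend three sessions a week for 18 months. The education arm attends every two weeks for 6 months and monthly after that. The Discussion notes a common belief that intense training may worsen knee pain.

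**Working it through.** **Inputs from the article.** 124 per group, 80% retention (0.8 × 124 = 99.2 per group), two-sided 0.0083 per primary comparison (0.05/6), 80% power, unadjusted two-sample t-test.

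**Inputs assumed.** Correlation *r* between baseline and 6 months; *r*² or *r*³ between baseline and 18 months (*r*³ is decay in calendar time). Outcomes have unit SD, so correlations are also slopes *b*6 and *b*18.

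**1. The plan's own figure.** Detectable *d* = (z(1−α/2) + z(0.80)) × √(2/99.2).
- At the secondary level 0.0167, *d* = 0.459, which reproduces the article's 0.46.
- At 0.0083, *d* = (2.640 + 0.842) × 0.142 = 0.494.
- The stated 17.6% and 9.6% cannot be checked, because no SD is given.

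**2. Variance with complete data.** With two visits and equal variances the shared slope is (*b*6 + *b*18)/2.
- Separate slopes: V = 1 − *b*18².
- Shared slope: V + (shared slope − *b*18)².

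| *b*6 / *b*18 | shared slope | V separate | V shared | increase |
|---|---|---|---|---|
| 0.6 / 0.216 | 0.408 | 0.953 | 0.990 | 3.9% |
| 0.7 / 0.343 | 0.522 | 0.882 | 0.914 | 3.6% |
| 0.8 / 0.512 | 0.656 | 0.738 | 0.759 | 2.8% |
| 0.7 / 0.49 | 0.595 | 0.760 | 0.771 | 1.5% |

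For *r* from 0.4 to 0.9 the increase is 0.6-1.7% under *r*² and 1.6-3.9% under *r*³.

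**3. Power at *d* = 0.494.** Power = Φ(3.482/√V − 2.640).
- At 0.6/0.216: 0.823 with separate slopes, 0.805 with the shared slope. This is the largest loss, 1.8 points.
- At 0.7/0.343: 0.857 against about 0.84.

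**4. Variance with 20% dropout at random.**
- Simulation of two arms of 124 (3,000 trials per setting): SD of the contrast, shared against separate, 0.1231 v 0.1213, 0.1342 v 0.1297 and 0.1296 v 0.1287 for correlations 0.8/0.51, 0.7/0.35 and 0.6/0.4. The squared ratios are 1.030, 1.071 and 1.014.
- A separate three-arm simulation (2,000 runs per setting) gave at most about 1.06 over all dropout patterns tried.
- Applying 1.071 to the 0.7/0.343 case: V = 0.882 × 1.071 = 0.945 and power = Φ(3.482/0.972 − 2.640) ≈ 0.83, a loss of about 3 points.

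**5. Bias.** True effect zero, about 20% dropout; in the three-arm simulation the logit of dropout changes by 1 per baseline SD. The main part of the bias is (shared slope − *b*18) × (difference between arms in completers' mean baseline). A smaller part in the same direction enters through the 6-month residuals. The table shows the three-arm simulation with 400,000 per arm, in SD units.

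| Dropout depends on baseline | shared slope | with baseline × visit |
|---|---|---|
| not at all, or alike in all arms | within ±0.005 | within ±0.005 |
| in one arm only | 0.017 to 0.042 | about 0 |
| in opposite directions in the two arms | 0.034 to 0.083 | about 0 |

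The two-arm simulation agrees: 0.022-0.032 and 0.045-0.065 with the shared slope, at most 0.003 in absolute size with the interaction.

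Plausibility check at 0.7/0.343: with that dropout model and a standard normal baseline, completers' mean baseline is −0.173 SD in an affected arm. One arm: (0.542 − 0.343) × 0.173 = 0.034, against 0.037 simulated. Opposite: (0.549 − 0.343) × 0.346 = 0.071, against 0.083.

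**6. What the bias does to the test.** Error rate ≈ Φ(−2.640 + q) + Φ(−2.640 − q), with q = bias/SE.
- One arm, largest: 0.042/0.142 = 0.30, giving about 0.011 against 0.0083.
- Opposite, largest: 0.083/0.1345 = 0.62, giving about 0.022.

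**The case against.** A reader might infer that the plan contradicts itself, because AR(1) correlation fades with time and so should weaken the baseline link at 18 months. The article does not support that. Baseline is a covariate and lies outside the repeated outcome vector, so AR(1) describes only the residuals at 6 and 18 months. With two visits it is a single correlation and carries no information about decay from baseline.

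A reader might also infer that any dropout related to baseline biases the contrast. It does not: when the relation is the same in every arm, the error cancels.

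The case for leaving the model alone has further substance. A main-effect baseline adjustment is conventional. The article projects 80% retention and gives no sign that baseline pain or force would drive loss differently by arm. The one-arm bias is about 0.3 of a standard error or less, and the larger figures need opposite dropout patterns. The 80% power rests on an unadjusted t-test, and with complete-data variances the shared-slope model matches or beats that except with weak, fast-fading correlations (0.788-0.790 against 0.800 at *r* = 0.4-0.5). All of this stands and limits the point to a small one.

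The remaining argument is that a condensed article may leave the term to a fuller plan. That is possible. But this article spells out its fixed effects, covariance structure, estimation method, contrast and significance level, and names one interaction. As written, the slope is shared. The promised checks concern distributions, variances and residuals. The alternative missing-data analyses are reserved for informative censoring, whereas this bias arises under missing at random.

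**Conclusion.** The point holds as a modest improvement to a stated specification. If the baseline link is weaker at 18 months, the shared slope costs 0.6-4% in variance with complete data and up to 6-7% with 20% dropout. That is about 2 power points on the complete-data variances, and about 3 at the largest simulated inflation.

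Against a detectable difference of 0.494 SD, a bias of 0.02-0.04 SD is about 4-8% (dropout related to baseline in one arm only), and 0.03-0.08 SD is about 6-16% (opposite directions).

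Every figure rests on assumed correlations, and the biases also on a fairly strong assumed dropout model; the article supplies neither. If the two slopes are equal, or if dropout relates to baseline alike in all arms, there is no bias to remove.

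**What to change.** Add baseline outcome × visit to the mixed model for knee pain and for maximal compressive force and, for consistency, to the other repeated outcomes that use the same model. State this before unblinded analysis. If a fuller analysis plan already has the term, a line saying so is enough.

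With the two visits named in the model the cost is one degree of freedom per outcome and no data. If the slopes turn out equal, the loss is negligible. In every scenario tried, the term brought the bias to about zero.

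BMI × visit and gender × visit are optional. Gender × visit and a continuous BMI × visit cost one further degree of freedom each; BMI entered as the five bands in the Randomization section would cost four.
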